**Fig. 1 Fig1:**
[figure not shown]
Assignment of interventions

### Qualitative sample

A purposive sample will be informed by learning from previous case studies of the National Age UK IPCP and will be targeted to ensure maximum variation to support further intervention optimisation—within the resource constraints of a feasibility study. We anticipate that this will be a mixture of client/carer dyads, those living alone and from different ethnic backgrounds.

### Trial consent or assent

Participant consent, recruitment and collection of baseline data will be undertaken in the potential participant’s own home by a researcher blind to cluster allocation. Home visits will be made to reduce participant burden and facilitate the assessment of capacity and cognition. Before consent researchers will make an assessment of the patient’s capacity to consent, using the Mental Capacity Act (MCA) framework (2005) [17]. Individuals lacking capacity to consent will not be excluded from this study as they may still benefit from engagement with the intervention. If a potential participant lacks capacity to consent, they will be asked to nominate a personal consultee to advise on their behalf. If the potential participant is unable to identify a personal consultee, the GP will be requested to identify an appropriate potential personal consultee. If a personal consultee is not available, no further contact will be made.

Following participant consent or consultee assent, researchers will administer the Montreal Cognitive Assessment (MoCA). Individuals scoring less than 10 will be deemed ineligible because they would be unable to take part in the shared decision making aspects of PCP. A carer will be identified (if available) and after consent; in the intervention arm, the practice administrative staff /PIC worker will be notified which patients have been registered.

Reasons for declining involvement will be noted if provided. The right of a patient (and carer) to refuse participation without giving reasons will be respected.

### The PROSPER intervention

PROSPER is a manualised intervention delivered to participants in their own home by trained Age UK Staff—Personal Independence Co-ordinators (PICs) and support workers (SW). It is based on the social cognitive theory (SCT) which resonates closely with the tenets of PCP in the context of frailty [18]. SCT specifies factors governing the acquisition of competencies that can profoundly affect physical and emotional wellbeing [19]. It identifies knowledge, skills, self-efficacy, outcome expectations, goals and concrete plans, and the perceived social and environmental facilitators and impediments as core determinants influencing health habits. Therefore, PROSPER targets confidence building and providing older people with knowledge and skills to set personal goals, develop appropriate action plans and personalised problem-solving strategies. PIC workers will undertake ‘guided conversations’ and shared decision-making, developing goals and action plans with older people. Support workers will practically support older people to achieve their goals. Both workers will be employed by a third sector organisation but work as part of a wider multidisciplinary team, co-located within a general practice.

Key intervention materials include the intervention manual and associated training package. The manual is divided into four sections: section 1 provides an overview of PCP, while sections 2 and 3 provide a guide on how to set up and deliver the service. Section 4 describes some of the key concepts which have shaped the development of PROSPER and includes a list of references for further information. Section 5 (the toolkit) contains the necessary templates of practical tools needed for set up and delivery of the PROSPER service, e.g. job descriptions, service invitation letters and action-plans. In addition, the manual contains a list of behavioural change techniques for use with older people identified in a systematic review.

The training package uses blended learning (including on-line, face to face and experiential delivery methods) and includes background to frailty, ‘the Art of the Guided Conversation’, motivational interviewing and a summary of behaviour change techniques for use with older people. Additional motivational interviewing training sessions enable reflection on the use of this approach after initial familiarisation in the field. Intervention training will take approximately 27 h.

Core intervention activities include a guided conversation to set personal goals and develop appropriate action plans; a two-month review to reflect on progress, problem solve, and confirm appropriate next steps; and ‘Graduation’ (discharge from service). In line with these activities, a minimum of three face-to-face contacts will be made. Additional face-to-face, telephone or email contact is expected within the 12-week intervention period. The amount of additional contact will vary depending on the needs of the older person.

We will continue to optimise the intervention using an iterative approach, with a focus on staff training, contextual factors and implementation in preparation for a definitive clinical trial.

### Consent to the process evaluation

All participants will be recruited to the process evaluation by an independent researcher not involved in baseline or follow-up data collection for the feasibility trial. Consent will be sought from each participating individual separate to the trial process. Identified clients will be sent an information booklet about the process evaluation at the same time as the invitation letter and intervention service information. The PIC worker will contact participants by telephone to explain the purpose of the observations and gain verbal consent for the process evaluation researcher to attend their first visit. Carers and significant others will also be asked for consent. Definitive consent for the PE will be sought by the independent researcher at the time of the PE data collection to avoid a significant time lapse between data collection and consent. In addition, we will seek specific consent for publication of any quotes and/or voice recordings for use in dissemination. Participants have the right to withdraw at any time and may withdraw from the process evaluation but continue in the trial.

### Usual care

Practices allocated to the control arm will continue to provide usual care, defined as ‘The wide range of care that is provided in a community whether it is adequate or not, without a normative judgement’ [20]. To increase external validity and relevance of trial findings to clinical practice, we will use an unrestricted usual care approach in both control and intervention arms in line with pragmatic trial design and the expected heterogeneity of available treatments [21]. It is also anticipated that some participants will receive disease-specific care planning for single long-term conditions. Use of specific services will be recorded at baseline and follow-up assessments and documented on case report forms (CRFs) or collected via routine data.

### Trial data collection

Participant outcome measures will be collected via (blinded researcher supported) self-completion questionnaires at baseline and postal follow-up questionnaires at 6 and 12 months. Prior to sending out the follow-up questionnaires, participant survival status and address will be confirmed. Supported completion, by a blinded researcher, at follow-up will be provided if a participant loses capacity during the trial. Researchers will receive training on all study specific assessments to ensure standardised completion and to monitor participant fatigue, which may necessitate data collection over multiple days.

Baseline and follow-up assessments will be ordered to prioritise primary outcome data. Participants will also receive a small unconditional monetary incentive (£10 gift voucher) to encourage follow-up at 12 months. We will additionally seek to promote participant retention through regular newsletters.

Participants, including carers, will be free to withdraw consent at any time. Where possible, clarification on the specific area of withdrawal, e.g. access to health and social care records will be sought, and the reason for withdrawal will be recorded, but not obligatory. Previously collected data will be used in the analyses.

### Process evaluation data collection

We will use a range of methods to explore intervention implementation across four intervention practices in two geographic localities. In addition to collecting primary data via non-participant observations, interviews and questionnaires, we will make use of secondary data sources wherever possible to reduce burden, i.e. CRFs from the trial and case reports from the Age UK delivery teams. Non-participant observations will be conducted, with consent, during delivery staff training, ‘guided conversations’, two month reviews, ‘graduations’ and MDT meetings. Semi-structured interviews will take place with delivery team staff: MDT members (in both control and intervention practices) and participants and their carers. In addition, we will use the NoMAD instrument [22] to describe how delivery and MDT staff view the intervention with reference to the four constructs of the normalisation process theory [23]. This will elicit views about how the intervention potentially impacts on their work and their expectations about whether it could become routine. It will also be used to identify any potential areas of training that need to be tailored to accommodate differences in each of the stakeholder groups. All observations and interviews will be audio or video recorded as appropriate.

### Outcome measures

A summary of assessments and outcome measures can be found in Table 1. If any assessment has been completed as part of usual care for a participant, the assessment will not be repeated for that participant for the purposes of the trial in order to minimise participant burden and the potential for recall bias.

[figure not shown]

**Table 1 Tab1:**
[figure not shown]
SPIRIT: summary and timing of assessments

Additional delivery team activity data such as type, number and duration of contacts will also be collected to identify the scope and reach of the intervention.

Data will be collected from practices and PIC teams during follow-up to determine if any change in practice has occurred during the study period and evaluate level of contamination.

### Sample size

Formal sample size calculations are not required for feasibility trials. However, based on PIC capacity, assuming 20% of patients will meet eligibility criteria and 33% of those will consent, we estimate an average of 25–50 patients per practice will participate in the study. A minimum of four clusters per arm is required to allow replication within study arm. We therefore aim to recruit up to 400 participants (200 per arm) from 11 clusters. A sample of this size will also allow us to estimate recruitment and follow-up rates with a maximum likely error of less than 10%. We originally planned to recruit from eight clusters in two geographic localities. However, funding was uncertain in one of the localities, and to avoid the risk of insufficient clusters, we increased the number of clusters in the funded locality. When funding became available in the second locality, the study team felt the addition of another four practices would elicit valuable contextual data for the process evaluation.

### Data management

All data will be analysed and securely stored at the CTRU. Only these data will be used in the analyses for all abstracts and publications relating to the questions posed within the study protocol—with the exception of process evaluation data. All analyses will be performed by the CTRU statistical team. All data will be stored for 10 years. Paper data will be disposed of with confidential waste, and electronic data no longer required for analysis will be deleted.

### Statistical methods

A single final analysis is planned after the trial is closed to recruitment and follow-up, and the trial database has been cleaned and locked. All analyses and data summaries will be conducted on the intention-to-treat (ITT) population [24]. Participants will be analysed according to the intervention they received. The analysis will focus on descriptive statistics and confidence interval (CI) estimation.

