### General practice recruitment and randomisation

A range of approaches will be used to engage with general practices including local National Institute for Health Research Clinical Research Networks (NIHR CRNs), professional networks and practices listed on the Public Health England (PHE) website [13].

Practices will be randomised on a 1:1 basis either to implement the intervention or continue with usual care (UC) only, using an algorithm for covariate-constrained randomisation to achieve balanced allocation between the trial arms on sample size and baseline characteristics expected to be potential confounding factors [14]. Randomisation will be performed by the statistical team at the Clinical Trials Research Unit (CTRU). Following randomisation, the CTRU will inform the practice manager of the allocation to allow trial procedures to be implemented. Knowledge of the allocation will be restricted to staff in the practice multidisciplinary team (MDT) who will be involved in the delivery of the intervention. MDTs may include a variety of staff from GPs to community matrons. We will seek to maintain blinding of practice staff not directly involved in intervention delivery. Instances of un-blinding will be recorded.

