### Participant recruitment/randomisation

To allow for scheduling of the intervention delivery and ensure that a similar number of participants are recruited from each general practice, eligible participants will be invited to consent to data collection in a phased approach. Following cluster randomisation, the CTRU will periodically generate a random sample of eligible participants to approach. Eligibility lists from each cluster will be ranked according to eFI to ensure a similar distribution of eFI scores that are randomly sampled across the clusters and between trial arms. For participants randomly sampled, eligibility will be re-confirmed by a practice staff prior to sending letters of invitation for trial participation (data collection). This process will be the same in both trial arms. PROSPER recruitment uses an opt-out approach, i.e. where an individual pro-actively declines to be contacted by a researcher by returning a negative expression of interest, to maximise potential for participant recruitment. This will allow researchers’ access to patient contact details after the opt-out period has ended and is aligned with previous research in this area [15, 16].

If there is no response to the invitation within 14 days, a researcher blinded to allocation will contact the potential participant by phone to discuss the study. If an individual is interested, the researcher will make an appointment to visit them. If not, the reason will be recorded, if possible. Once a participant is registered in the study, the Age UK delivery team will receive notification of those in the intervention arm and proceed to make contact. Participants in the control arm will continue to receive usual care.

The process for assignment of interventions is outlined in Fig. 1.

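### The Statistical methods section promises intention-to-treat and then groups participants by intervention received; the two rules conflict and the second needs correcting

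*Protocol article*

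**What the plan says.** Two consecutive sentences in the Statistical methods section of the protocol article set the analysis rule. The first is "All analyses and data summaries will be conducted on the intention-to-treat (ITT) population". The second is "Participants will be analysed according to the intervention they received". The second carries no qualifier: it is not tied to a per-protocol, secondary or sensitivity analysis. The same section provides for one analysis only: "A single final analysis is planned after the trial is closed to recruitment and follow-up".

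Allocation is by cluster. Under General practice recruitment and randomisation, "Practices will be randomised on a 1:1 basis either to implement the intervention or continue with usual care (UC) only". Individuals join afterwards. Under Participant recruitment/randomisation, "eligible participants will be invited to consent to data collection in a phased approach", and only once a person is registered does it follow that "the Age UK delivery team will receive notification of those in the intervention arm and proceed to make contact".

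Results to be reported by arm include timing and reasons for withdrawal (Screening, recruitment and follow-up). They also include data completeness, outcome summaries and 12-month confidence intervals for the difference between arms (Feasibility and acceptability of outcome measures and methods of data collection).

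**The concern.** Intention-to-treat in a cluster trial means that each participant is counted in the arm to which the practice was randomised, whatever care followed. Grouping by what was received is a different rule. An analyst given both sentences has no stated basis for choosing between them.

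Taking up PROSPER happens after randomisation and may well be related to the reasons for which people withdraw, fail to return questionnaires or report poorer health. If receipt defines the groups, people in intervention practices who never engage are no longer analysed as randomised. The comparison of withdrawal between arms, which the article wants to examine for effects attributable to the intervention, would then partly compare engagers with non-engagers. Completeness, outcome summaries and the 12-month intervals are exposed in the same way. If non-receivers were moved to control, a single practice would also contribute to both groups, which no longer matches the cluster design.

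**Working it through.** **Step 1: set the two rules side by side.** The first sentence takes in all analyses and summaries and names intention-to-treat, so grouping is by allocation. The second applies to participants without restriction and groups by receipt. With one planned analysis, the second sentence cannot be assigned to a separate secondary analysis.

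**Step 2: can the groupings differ here?** Yes. The order is practice randomised, participant consents to data collection, participant registered, delivery team makes contact. Enrolment does not depend on receiving the service. The article also plans to evaluate contamination, so receipt outside the intervention arm is contemplated too.

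**Step 3: illustrate the size.** The article gives no uptake rate and no by-arm return rates, so there is no figure of its own to reproduce. The target of 200 per arm comes from the Sample size section. Everything else is assumed: non-engagement u = 25% (50 of 200), and 12-month return of 80% in engagers, 50% in non-engagers and 75% in controls.

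- By allocation: intervention (150 × 0.80 + 50 × 0.50)/200 = 145/200 = 72.5%; control 75%. Difference **-2.5 points**.
- Non-engagers moved to control: intervention 120/150 = 80%; control (200 × 0.75 + 50 × 0.50)/250 = 175/250 = 70%. Difference **+10 points**.
- Non-engagers dropped: 80% v 75%. Difference **+5 points**.

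**Step 4: vary the assumptions.** With the same return rates and different non-engagement:

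| u | By allocation | Moved | Dropped |
|---|---|---|---|
| 10% | +2.0 | +7.3 | +5.0 |
| 25% | -2.5 | +10.0 | +5.0 |
| 30% | -4.0 | +10.8 | +5.0 |

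Now hold u at 25% and let g be the gap in return, in points, between engagers (80%) and non-engagers (80% - g). By allocation the difference is 5 - 0.25g. Moved, it is 80 - [200 × 75 + 50 × (80 - g)]/250 = 4 + 0.2g. Dropped, it stays at 5.

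| g (points) | By allocation | Moved | Dropped |
|---|---|---|---|
| 0 | +5.0 | +4.0 | +5.0 |
| 10 | +2.5 | +6.0 | +5.0 |
| 20 | 0.0 | +8.0 | +5.0 |
| 30 | -2.5 | +10.0 | +5.0 |

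The sign reverses only when g exceeds 20 points. The rules disagree over most of the range, but the reversal comes from the chosen gap.

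**Step 5: a continuous outcome with no true effect.** Suppose non-receivers score d SD worse than receivers and the control arm has the same mix. With the arm mean at 0, receivers average ud and non-receivers ud - d. If non-receivers are moved, the spurious difference is 2ud/(1 + u). If they are dropped, it is ud. For d from 0.3 to 0.5:

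- u = 10%: moved 0.06/1.1 = 0.055 to 0.10/1.1 = 0.091 SD; dropped 0.03 to 0.05 SD.
- u = 40%: moved 0.24/1.4 = 0.171 to 0.40/1.4 = 0.286 SD; dropped 0.12 to 0.20 SD.

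By allocation the difference is 0 throughout.

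**The case against.** The strongest reply is that this is a slip for the word allocated. The first sentence is comprehensive and names intention-to-treat. Elsewhere the article uses arm in the sense of allocation: the Usual care section ties the control arm to how practices were allocated, and the recruitment section has the delivery team told who is in the intervention arm before any contact. Because the intervention is described as delivered at practice level, received could also loosely mean the service assigned to the practice.

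Much of this stands. A reader might infer that every by-arm result will be as-treated. The article does not support that, because it requires the second sentence to override the first. A reader might also infer that non-uptake would be hidden. That is not supported either: type, number and duration of contacts are to be collected (text with Table 1), and uptake is to be reported under Intervention delivery. Nor does any section say that non-receivers would be moved to control or excluded; those are the two obvious ways of applying the sentence.

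The stakes are also bounded. This is a feasibility trial with descriptive statistics, interval estimates and no formal testing. Overall recruitment is unaffected by grouping, and nothing available shows an effect on the progression decision.

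What does not stand is the idea that the sentence can be left alone. Its plain meaning is the opposite of intention-to-treat, and no other section expressly corrects it. Reading the first sentence as fixing who is included and the second as fixing how they are grouped does not help: everyone would be kept but classified by receipt.

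**Conclusion.** The section contradicts itself, and its second sentence, as worded, is the wrong grouping rule for an intention-to-treat analysis of a cluster-randomised trial. This conclusion rests on the text alone and needs no assumed figure.

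The consequence is conditional. If the second sentence were followed, the by-arm withdrawal, retention, completeness and outcome summaries and the 12-month intervals could be biased. The sizes shown (-2.5 points by allocation against +10 or +5 by receipt, or a spurious 0.03 to 0.29 SD under no effect) indicate what is possible under assumed uptake, return rates and differences between receivers and non-receivers. They are not predictions for this trial, and the change of sign depends on those inputs. The analysis plan, which is not available here, may state the rule correctly; the article's sentence would still be wrong.

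**What to change.** Replace the second sentence with: *Participants will be analysed in the arm to which their cluster was randomised, whether or not they received any PROSPER contact.* Label any summary by receipt as supplementary, and carry the same wording into the analysis plan. The uptake and contact reporting already planned can stay as it is. The cost is one sentence, with no new data, no extra participants and no change to trial conduct.
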